### Data management

Data must be reported on eCRF. All protocol-required information collected during the trial must be entered by the investigator or authorised staff members as soon as possible after information is collected. Any outstanding entries must be completed immediately after the final examination. It is the responsibility of the investigator to review and sign the eCRFs.

### Compliance/rate of loss to follow-up

In order to maximise the number of participating patients to the study, disabled patients may be visited by a “flying study nurse”. Phone interviews are only exceptionally allowed.

A rate of 10–20 % of drop-outs and losses to follow-up are considered in order to have a sufficient power in the per-protocol analysis.

### Safety assessments and reporting of adverse events

Analysis of safety-related data is performed by calculation and descriptive comparison of the rates of AEs and serious adverse events (SAEs) based on all patients receiving at least one protocol-specified procedure.

An AE is defined as any untoward medical event in a patient which occurs following surgery or chemotherapy. A SAE is defined as any AE that results in death, immediately life threatening event, hospitalisation or prolongation of hospitalisation, persistent or significant disability or incapacity. SAEs will be classified according to intensity (mild, moderate, severe, life-threatening, death), outcome (recovered completely, recovered with sequelae, not recovered with or without therapy of SAE, death, unknown), and causality (doubtful, possibly related, probably related, definitely related, not assessable).

The investigator must report every event meeting the protocol definition of an SAE to the coordinating investigator until the next working day after having become aware of the event.

### Statistical methods

#### Sample size calculation

The sample size calculation is based on the analysis of the primary endpoint, completeness of adjuvant chemotherapy. According to our recent randomised phase III trial on perioperative treatment of stage II and III rectal cancer, a total of 61.7 % (capecitabine) and 57.5 % (5-FU), respectively, started adjuvant chemotherapy, and 45.7 and 40.0 % had their scheduled cycles completed [14]. These data are consistent with the findings in other studies investigating perioperative chemo (radio)therapy in rectal cancer.

Based on this data, we assume a CoC rate of 42 % for the standard patient group with a diverting stoma during adjuvant chemotherapy. A 20 % absolute increase of CoC (42–62 %) is regarded as a clinically meaningful step forward. In order to significantly detect this difference on a type I error level of 5 % (two-sided) with a power of 80 %, a sample size of 107 is required in each arm based on the application of Fisher’s exact test. The Mantel-Haenszel procedure stratifying for centre will be used for the primary hypothesis of the trial.

Any major deviation from these CoC rate assumptions will lead to increased power, if the delta of 20 % is retained. According to the primary endpoint, the number of losses in the intention-to-treat (ITT) population should be minimal. A rate of 10–20 % of drop-outs and losses to follow-up is expected. Thus, about 260 patients should be randomised to ascertain sufficient power in the per-protocol analysis. Stratification by centre is foreseen, since centre-specific characteristics such as the quality of surgery, patient guidance with respect to chemotherapy compliance, etc. may have a major influence on important outcome parameters.

#### Definition of analysis population

Patients who were enrolled although they unequivocally did not fulfil the selection criteria of the trial a priori (“non-eligible”) will be excluded from the statistical analysis, in accordance with ICH recommendations [26].

All other patients will primarily be evaluated in an ITT analysis according to allocation by randomisation. A second analysis (“per protocol”) of the primary endpoint will include only patients with full documentation on the amount of adjuvant chemotherapy received (i.e. including patients with a reliable documentation of no or incomplete adjuvant treatment).

All patients having received at least one application of protocol-defined therapy are evaluable for safety.

#### Analysis variables and statistical methods

Primary analysis

The character of the primary analysis is confirmatory. The analysis is based on the ITT population using the ITT principles (dropouts and missing data will be counted as failures). For the analysis of the primary endpoint, the Mantel-Haenszel stratified test will be used. Corresponding 95 % confidence interval (CI) will be calculated for the CoC rates in both groups and for the rate difference and odds ratio (OR).Sensitivity analysis

The primary endpoint will be additionally analysed based on the per-protocol set comprising all patients with full documentation on the amount of adjuvant chemotherapy received. A multivariate analysis (logistic regression model) will be applied to account for the effect of potential prognostic factors such as for example age, performance status, location of the primary tumour, and T-stage.Secondary analysis

All secondary analyses have only exploratory character. P-values may only be used descriptively. All variables will be described at least by the number of observations, mean, standard deviation, median, minimum and maximum, or counts/percentages, as appropriate.

QoL data will be scored according to the algorithm described in the EORTC QLQ-C30 scoring manual [27]. While data on all functional and symptoms scales will be described, formal comparisons are going to focus on global QoL and symptoms related to the impact of chemotherapy and surgery on rectal cancer patients specifically (overall QoL, diarrhoea, constipation, vomitting).

In case of disease-free survival, local recurrence-free survival and distant recurrence-free survival Kaplan Meier survival curves for the groups will be presented and compared by the log rank test. Further secondary endpoints will be compared using a Wilcoxon-Mann–Whitney-U test or tests for contingency tables, as appropriate according to the type of data.

No interim analysis is planned. However, while the main statistical analysis is performed, as soon as documentation of post-operative therapy is completed in all patients at about 7 months post randomisation, a second analysis on long-term endpoints is performed about 1.5 years later.

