## Background

Low anterior resection (LAR) is the procedure of choice for rectal cancer of the middle and lower third [1, 2]. An anastomosis performed close to the pelvic floor is associated with a relevant risk of anastomotic leakage (3–17 %), which contributes to mortality [3]. Based on level-1 evidence a diverting stoma effectively reduces the rate of symptomatic anastomotic leakage [4].

However, a diverting stoma also causes morbidity, which may affect nearly half of all patients as shown in an analysis of patients with protective stoma for distal colonic anastomosis [5]. Stoma-related morbidity includes high-output stoma, stoma prolapse, small bowel obstruction and wound infection and has been evaluated in several studies [5–7]. Moreover, a stoma may impair quality of life (QoL). The global QoL as well as the physical functioning and role scores are negatively influenced by stoma after LAR with total mesorectal excision (TME) as shown in two prospective observational longitudinal studies of 22 [8] and 24 patients [9] respectively. These scores and additionally the mental health improved 6 weeks after ileostomy closure. Contrarily, 23 patients receiving a high anterior resection without stoma had higher QoL scores postoperatively compared to preoperatively [9].

Very little evidence regarding the optimal timing for stoma closure was found despite an extensive systematic search in relevant literature databases and trial registries. Our prospective multicentre pilot study investigating the timing of stoma closure and longitudinal QoL before LAR with TME, before stoma closure and 6 months after stoma closure on 171 patients from 17 participating German surgical centres showed that this is in median performed 5.1 months after creation, with a wide range (0.6–32 months) [10].

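### For the quality-of-life scales picked for formal comparison, the only fitting test named is an unadjusted Wilcoxon test without a between-arm estimate; if a pre-randomisation score exists, a baseline-adjusted model would be more precise

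*Protocol article*

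**What the plan says.** All points below are from the protocol article, section Analysis variables and statistical methods, unless stated otherwise.

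- Quality of life is scored with the QLQ-C30 manual, and "formal comparisons are going to focus on global QoL and symptoms related to the impact of chemotherapy and surgery on rectal cancer patients specifically". The scales listed are overall quality of life, diarrhoea, constipation and vomiting. This paragraph names no test.
- The next paragraph gives Kaplan-Meier curves and the log-rank test to three recurrence-type endpoints, and then: "Further secondary endpoints will be compared using a Wilcoxon-Mann–Whitney-U test or tests for contingency tables", the choice between them depending on the data type.
- The status of these analyses is explicit: "All secondary analyses have only exploratory character. P-values may only be used descriptively".
- The one covariate-adjusted model in the article concerns the binary primary endpoint: "A multivariate analysis (logistic regression model) will be applied to account for the effect of potential prognostic factors". The primary endpoint also gets 95 % confidence intervals for the rate difference and the odds ratio.
- A quality-of-life measurement before surgery is described only for the group's pilot study, in the Background: "longitudinal QoL before LAR with TME, before stoma closure and 6 months after stoma closure". For CoCStom itself, example visit plans and the definitions of secondary endpoints are in additional files that are not shown.

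**The concern.** Quality of life heads the list of secondary endpoints in the abstract, and the effect of a stoma on it is one of the trial's motives. QLQ-C30 scores usually differ between patients in a lasting way, so part of the spread at follow-up can be predicted from an earlier score. A two-sample rank test on follow-up scores leaves that part in the error term.

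The second issue is what the test delivers. Where p-values are only descriptive, the useful product is an estimated difference with its uncertainty. The Wilcoxon test as named gives a p-value. Means and standard deviations per arm are promised, but no between-arm difference with an interval. The Background shows the limit of this: the earlier randomised trial of 186 patients is summarised for quality of life as showing no difference, with p = 0.566. That figure alone does not tell the reader whether a relevant difference was excluded or merely not detected.

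**Working it through.** **The plan's own figure.** The article gives no power for any score endpoint, only 107 per arm for the primary endpoint (42 % against 62 %, two-sided 5 %, power 80 %, Fisher's exact test). The usual formula is n = [1.96·√(2·0.52·0.48) + 0.8416·√(0.42·0.58 + 0.62·0.38)]² / 0.20² = (1.385 + 0.583)² / 0.04 ≈ 96.8, so 97. With the continuity correction, (96.8/4)·[1 + √(1 + 4/(96.8·0.20))]² ≈ 106.5, so 107. Exact enumeration of Fisher's test gives 79.6 % power at 107 per arm and 80.2 % at 108. The figure reproduces, and 107 per arm is used below. This assumes quality-of-life data as complete as the primary endpoint.

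**Inputs not in the article (assumed).** Correlation r between pre-randomisation and follow-up score: 0.3 to 0.6. Difference: 8 points. SD: 22. Scores normally distributed.

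**Variance.** Relative to a comparison of follow-up means, adjustment multiplies the error variance by 1 − r². Analysing changes multiplies it by 2(1 − r). The equivalent gain in patients from adjustment is 1/(1 − r²) − 1.

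| r | Adjusted, 1 − r² | Change, 2(1 − r) | Equivalent gain in patients |
|---|---|---|---|
| 0.3 | 0.91 | 1.4 | 10 % |
| 0.4 | 0.84 | 1.2 | 19 % |
| 0.5 | 0.75 | 1.0 | 33 % |
| 0.6 | 0.64 | 0.8 | 56 % |

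Since 2(1 − r) − (1 − r²) = (1 − r)², adjustment is never worse than a change score. The direction of the point therefore does not depend on which quantity the plan means to rank. Its size does: a change score already recovers some precision when r exceeds 0.5, and loses some when r is below 0.5.

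**Power by normal approximation.** The standardised difference is 8/22 = 0.364, and 0.364·√(107/2) = 2.66.

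- Unadjusted comparison of means: Φ(2.66 − 1.96) = 75.8 %.
- Wilcoxon on follow-up scores, with relative efficiency 3/π under normality: 2.66·√(3/π) = 2.60, and Φ(2.60 − 1.96) = 73.9 %.
- Adjusted, 2.66/√(1 − r²): 2.79, 2.90, 3.07 and 3.32 for r = 0.3, 0.4, 0.5 and 0.6, giving 79.6 %, 82.7 %, 86.7 % and 91.4 %.

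A simulation with 3000 runs per value of r gave 72 % to 74 % for the Wilcoxon test and 79 %, 82 %, 85 % and 92 % for the adjusted model, in line with these values.

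**What the baseline itself contributes.** At r = 0.3 the gain is 79.6 − 73.9 = 5.7 percentage points. Of these, 75.8 − 73.9 = 1.9 come from replacing a rank test by a comparison of means under assumed normality, and 79.6 − 75.8 = 3.8 from the baseline score.

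**Interval.** The 95 % half-width is 1.96·22·√(2/107) = 5.9 points unadjusted. It becomes 5.9·√0.91 = 5.6 at r = 0.3 and 5.9·√0.64 = 4.7 at r = 0.6.

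**The case against.** A fair defence has several parts.

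- **The test is not tied to follow-up values.** A reader might infer that the plan ignores each patient's earlier score. The article names a test but not the quantity tested, so changes from baseline are not excluded. This stands: the plan cannot be charged with discarding the baseline.
- **Quality of life has its own paragraph without a test.** The sentence on further endpoints could be meant for everything else, which would leave the quality-of-life method open. This stands in part. The link to the Wilcoxon test is an inference, but a strong one, because formal comparisons are announced and no other named test fits a score.
- **A pre-randomisation score is not documented.** A reader might take the pilot study's measurement before surgery as evidence that CoCStom has one too. It is a separate study. Without such a score no precision is given up. This stands and makes the point conditional.
- **The size is assumed.** Nothing in the article supports r = 0.5 or 0.6 between a score taken at or before day 7 after resection and one taken months later, after chemotherapy. Three of the four scales are symptom scales with coarse values, where a rank test is defensible and normal-theory figures are least reliable. This stands too.
- **The analysis is exploratory.** A reader might conclude that the trial is underpowered for quality of life or will miss a real effect. No power is claimed for it, and under randomisation chance imbalance at baseline adds variance, not bias. What remains is the case for an estimate with an interval, which an exploratory status strengthens.
- **Modelling detail belongs in the analysis plan.** True for covariates and visit handling in general. Here, however, the article does name a test, and a better one can be named in its place.

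**Conclusion.** The point holds as a small, conditional improvement. For the four QLQ-C30 scales, the only fitting test named is unadjusted and comes without a between-arm estimate and interval. If a pre-randomisation score is collected, a baseline-adjusted model is the better main analysis. The gain runs from modest (9 % less error variance at r = 0.3, about 6 points of power in the example) to material (36 % at r = 0.6, about 17 points). Those figures rest on an assumed correlation, SD, difference and normal scores, and on the Wilcoxon test being applied to follow-up scores.

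The article does not support saying that available baseline data are discarded, that the named test is invalid, or that the quality-of-life comparison fails a stated power target. Endpoints without a baseline value, such as days in hospital, are not concerned. The primary analysis and the sample size are untouched.

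**What to change.** Provided a QLQ-C30 score is taken before randomisation, state for the scales listed for formal comparison:

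- The main analysis is a linear model of the follow-up score on arm and the last pre-randomisation score, or a mixed model for repeated measures if several visits are used.
- The result reported is the adjusted mean difference with its 95 % CI, still labelled exploratory.
- The Wilcoxon test is kept as a supportive check, particularly for the coarse symptom scales, and the quantity it is applied to (follow-up score or change) is stated.

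The cost is analysis wording and a short piece of programming. There is no consequence for error rates, because these p-values are descriptive. If no pre-randomisation score is collected, the recommendation to adjust lapses. Introducing a new questionnaire for this purpose is not proposed: 75 patients had already been randomised by August 2015 and could not supply a score from before randomisation.

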### Individual trial termination

Patients may be withdrawn from the trial any time at their own request without giving reasons for their decision or if, in the investigator’s opinion, continuation of the trial would be detrimental to the patient’s well-being.

### Premature closure of the trial

The trial may be prematurely closed by the principal investigator in consultation with the steering committee. If the termination of the trial becomes necessary, the steering committee will discuss this issue with the independent data safety and monitoring board (DSMB). Reasons that may necessitate a termination of the trial include a potential health hazard caused by the trial treatment indicated by incidence or severity of SAEs in this trial, unsatisfactory patients’ enrolment, severely inaccurate and/or incomplete data recording or external evidence demanding a termination of the trial. The Ethic Committees will be informed.

### Trial organization and administration

#### Monitoring

All participating centres were personally trained and introduced into study-specific procedures during initiation visit. Regular on-site monitoring visits are planned at all sites. For at least 5 % of all subjects a 100 % clinical source data verification (SDV) for all clinical items is planned. The extent of further SDV and/or the frequency of monitoring visits will be adapted for individual centres depending on the quality of data or if common protocol violations are observed. In addition to the SOPs and to the trial protocol, procedures will be predefined in a study-specific monitoring manual and an eCRF manual. Queries will be issued by the monitor as well as the data manager and have to be answered by the investigators within a short time to avoid errors in data capture or entry being carried forward.

#### Steering committee

The steering committee supervises the conduct of the trial and issues recommendations for early termination, modifications or continuation of the trial, if necessary. It comprises seven members (three surgeons, two oncologists, radio-oncologist and statistician).

#### Data and safety monitoring board (DSMB)

To enable an independent risk assessment for treatment, potentially related SAEs will be noted and periodically (at least once a year during the first 24 months) assessed by the independent DSMB. Clinical monitoring will supervise patient’s safety and integrity of the clinical data. DSMB is an independent committee of 3 members (a surgeon, a radio-oncologist, and a statistician) whose task is to review the status of the clinical trial and make recommendations to the clinical research group concerning trial conduct, modification and/or publication. DSMB members will be asked to give advice on whether the accumulated safety data − notably SAEs − from the trial, together with results from other relevant trials, justify continuing recruitment of further patients. A decision to discontinue recruitment, in all patients or in selected subgroups, will be made only after discussion of the issue with the steering committee.

#### Ethical and legal aspects

The trial protocol, informed consent document and all trial specific documents were approved by the Ethics Committee II of the Medical Faculty of Mannheim, University of Heidelberg. Additionally, an ethical approval has been obtained at all participating centres (Additional file 4). The responsible investigator will ensure that this study is conducted in agreement with the Declaration of Helsinki (Tokyo, Venice, Hong Kong, Somerset West, Edinburgh, Seoul and Fortaleza amendments) [28] and the laws and regulations of the country. The protocol has been written, and the trial will be conducted according to the principles of ICH Harmonized Tripartite Guideline for Good Clinical Practice [26]. Patient data in the eCRF will be pseudonymised.

#### Benefit-risk assessment

Benefit-risk assessment was critically reviewed. Potentially, early stoma closure could result in more clinically relevant leaks of the rectal anastomosis as the time period for complete anastomotic healing is shorter. In order to exclude or minimize the risk of developing a clinically relevant leak of the rectal anastomosis after stoma closure the appropriate investigations confirming a healed anastomosis, which are usually done before late stoma closure, are mandatory also for early stoma closure. Several studies, including a large randomized controlled study, have not shown an increased risk for symptomatic leaks of the rectal anastomosis after early stoma closure [6, 8, 11]. Healing of the small bowel anastomosis after stoma closure may be impaired in the early group, because tissues may still be more friable such a short time after laparotomy. Again, several studies, including a large randomized controlled study, have not shown an increased complication risk for patients undergoing early stoma closure. On the other hand stoma closure may be more easy and faster as scaring may not yet be so pronounced less than ten days after stoma creation. Moreover, multiple complications may occur after stoma placement (e.g. kidney failure, prolapse, etc.), which may be minimized by early stoma closure. Finally, early stoma closure may have an impact on CoC potentially resulting in more patients receiving the full or at least a higher dose of scheduled chemotherapy which in turn could improve the oncological prognosis. Several studies including an analysis of our own data within a randomized controlled trial have shown that incomplete chemotherapy cycles and reduced dosages influence oncological outcome [14, 29, 30]. Therefore, even if a small to moderate increase of complications occurred due to early stoma closure this may be acceptable in order to improve overall outcome of patients.

## Discussion

Whether the time point of stoma closure influences the complete administration of the planned adjuvant chemotherapy, in patients with locally advanced rectal cancer undergoing LAR with TME after neoadjuvant therapy, remains unclear. Besides local complications stoma can have a negative impact on the patient’s psychological state since the mental health score was shown to be impaired in the presence of a stoma [9]. After tumour resection, stoma has a significant influence on the patients’ well being [9], affects them emotionally [8] and thus has a major impact on their compliance with the treatment. Some patients insist on stoma closure before the end of adjuvant chemotherapy cycles which may lead to a delay of the remaining therapy and may also increase complication rates [7]. Other patients stop therapy prematurely due to presence of a stoma [31].

That early stoma closure is an important issue in the complex therapy of rectal cancer patients is confirmed also by a newly started prospectively randomised Scandinavian multicentre study [32]. It compares early closure versus standard treatment (8–13 days vs. 12–26 weeks after surgery) with postsurgical morbidity as primary endpoint, QoL and the socio-economic effects of early closure as secondary endpoints. But this trial does not investigate CoC which therefore will remain an open question with high clinical relevance for the individual patient.

It is of major importance that patients undergo all chemotherapy cycles in order to maximally benefit from adjuvant treatment [30] but several studies show that not all patients are able to receive all cycles of the planned adjuvant therapy [14, 29, 30]. This may be due to suboptimal compliance with the therapy which can be explained by chemotherapy toxicity and postoperative complications.

Since early stoma closure is possible without increase in preoperative mortality and the complete administration of the planned chemotherapy cycles potentially improves the oncological outcome, it remains to be determined how early stoma closure influences CoC. This is the primary goal of the CoCStom trial and will contribute to clarifying how the largest benefit from adjuvant therapy can be gained for the affected patients. Therefore, CoC is a suitable primary endpoint and has high clinical relevance for the individual patient.

The trial may also have relevant socio-economic impact as early closure, if shown as equivalent or even superior, can cut costs due to reduced need for stoma care products and also due to a shorter overall period of hospitalisation.

CoCStom is a combined surgical-oncological trial. Its success requires a very good collaboration between surgeons and oncologists and the results may also have an impact on current guidelines as early closure of a stoma is currently not regarded as standard of care. Furthermore, results may also influence the “German DRG-System” on which is based the financing of medical in-house procedures. Presently, ileostomy closure within the same hospital stay as the rectal resection is not additionally reimbursed in contrast to late stoma closure in a second hospital stay.

